**Primary outcome measures**							
**Adherence**							
Clinic-based adherence to physiotherapist’s recommendations			#	#	#	#	
General adherence to physiotherapist‘s recommendations				✓	✓	✓	✓
Specific adherence to back exercises and physical activity advice				✓	✓	✓	✓
**Physical Activity**							
Self-reported physical activity		✓		✓	✓	✓	✓
**Low Back Pain Symptoms**							
Pain Intensity		✓			✓	✓	✓
Bothersomeness		✓			✓	✓	✓
**Pain-related Function**							
Disability		✓			✓	✓	✓
Patient specific function		✓			✓	✓	✓
**Pain-related Well Being**							
Quality of life		✓			✓	✓	✓
**Secondary Outcomes**							
Autonomy support from physiotherapist			*✓		✓		
Fear avoidance beliefs regarding physical activity		✓			✓	✓	✓
Perceived competence regarding ability to follow physiotherapist’s recommendations		✓	✓		✓	✓	✓
Autonomous and controlled motivation to following physiotherapist’s recommendations		✓	✓		✓	✓	✓
Objectively measured physical activity				✓	✓	✓	✓
Perception of recovery		✓			✓	✓	✓
**Moderating Variables**							
Expectation of treatment	*		✓				
Patient depression		✓					
Physiotherapist’s general causality orientations	*						
Physiotherapist’s autonomous and controlled motivation for participation in training.	*						

Note: ✓ = patient rated assessment. * = physiotherapist rated assessment. # = physiotherapist rating of patient behavior following each treatment session (most likely to occur during first 12 weeks following initial session).

##### Follow-up assessments (Week 1)

At week 1, after the patient’s initial physiotherapy session, he/she will be contacted by a blinded researcher to record the pedometer step count for the previous seven days, self-reported PA, and adherence. This will be done by a telephone call or an email, depending on the patient’s preference (provided at the time of recruitment). At this time, the patient can ask any questions regarding the use of their pedometer or any other general questions pertaining to their involvement in the study.

##### Follow-up assessments (Weeks 4, 12, and 24)

Follow-up outcome measures at Weeks 4, 12, and 24 will be collected via one of three methods, depending on patient preference; (i) over the telephone with a blinded research investigator, (ii) online questionnaire or (iii) hardcopy of the questionnaire sent via post with a pre-paid return envelope. Attempts to ensure complete follow-up data is collected on time will involve; (i) pre-posting the follow-up questionnaire to the patient 1 week before it is due with a pre-paid self-addressed return envelope for easy return postage, (ii) sending a text message to let the patient know the follow-up assessment has been posted, (iii) the Research Physiotherapist telephoning the patient during the week the assessment is due to ensure the patients has received the questionnaire and answer any questions he or she may have. In situations where the assessment is overdue by two weeks, the Research Physiotherapist will contact the patient by telephone and, if contact is not made, she will send a handwritten letter asking the patient to complete and return the questionnaire.

### Outcomes

A brief description of the outcomes is listed below. The timeline of assessments is detailed in Table 3. Detailed descriptions and references for these measures are presented in Appendix A.

#### Primary outcome measures

(i) *General adherence to physiotherapy recommendations*, during the therapy session as rated by the physiotherapist [adapted version of Sports Injury Rehabilitation Adherence Scale] and outside the clinic as rated by the patient [Adherence to Physiotherapists’ Recommendations Scale]. We will also collect information regarding the patient’s recall and adherence to recommendations regarding specific back exercises and PA using an adapted version of a Home Exercise Compliance Assessment.

(ii) *PA level,* self-reported using the International Short Form Physical Activity Questionnaire.

(iii) *Back Pain Symptoms, Function and Well Being,* measured by Pain Intensity [Numerical Rating Scale], Pain Bothersomeness, the Roland Morris Disability Questionnaire, the Patient Specific Functional Scale, the European Quality of Life Questionnaire, and the Perception of Recovery Scale.

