**Methods/Design:**

This study will be a single-blinded cluster randomized controlled trial. Outpatient physiotherapy centers (*N* =12) in Dublin, Ireland (population = 1.25 million) will be randomly assigned using a computer-generated algorithm to either the experimental or control arm. Physiotherapists in the experimental arm (two hospitals and four primary care clinics) will attend eight hours of communication skills training. Training will include handouts, workbooks, video examples, role-play, and discussion designed to teach physiotherapists how to communicate in a manner that promotes autonomous patient motivation. Physiotherapists in the waitlist control arm (two hospitals and four primary care clinics) will not receive this training. Participants (*N* = 292) with chronic low back pain will complete assessments at baseline, as well as 1 week, 4 weeks, 12 weeks, and 24 weeks after their first physiotherapy appointment. Primary outcomes will include adherence to physiotherapy recommendations, as well as low back pain, function, and well-being. Participants will be blinded to treatment allocation, as they will not be told if their physiotherapist has received the communication skills training. Outcome assessors will also be blinded.

We will use linear mixed modeling to test between arm differences both in the mean levels and the rates of change of the outcome variables. We will employ structural equation modeling to examine the process of change, including hypothesized mediation effects.

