### Hypotheses

1. Patients in the experimental arm will report significantly greater weekly physical activity (PA) participation compared with their pre-treatment PA levels and compared with patients in the control arm. They will also report greater self-rated adherence to physiotherapists’ recommendations compared with the patients in the control arm. Compared with physiotherapists in the control arm, physiotherapists in the experimental arm will rate their patients as more adherent during physiotherapy sessions.

2. Patients in the experimental arm will report significantly decreased pain, increased function, greater low back pain (LBP)-related well-being and greater perceived global improvement after treatment compared with their pre-intervention scores, and compared to patients in the control arm.

3. Compared with their pre-treatment scores and compared with patients in the control arm, patients in the experimental arm will report significantly lower fear-avoidance beliefs and controlled motivation, as well as significantly greater competence and autonomous motivation.

4. Patients in the experimental arm will rate their physiotherapists as significantly more autonomy supportive than patients whose physiotherapists were assigned to the control arm. As a result of heightened self-awareness that comes from participation in communication skills training, physiotherapists assigned to the experimental arm will rate themselves as less autonomy supportive than physiotherapists assigned to the control arm. Independent raters of audio recordings of patient-physiotherapist interactions will rate experimental arm physiotherapists as more autonomy supportive than physiotherapists assigned to the control arm. Physiotherapists in the experimental arm will employ the specific communication strategies taught in the workshops with higher quality than physiotherapists from the control arm (who will not attend these workshops).

5. The influence of the experimental manipulation on outcomes (pain, function, and well being) will be mediated by patients’ rating of the physiotherapist’s autonomy support, perceived competence, autonomous motivation, fear-avoidance beliefs and adherence (see Figure 2).

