## Methods/Design

### Design overview

This study will be a single-blinded cluster RCT. Physiotherapists in the experimental arm (two hospitals and four primary care clinics) will attend eight hours of communication skills training. Physiotherapists in the waitlist control arm (two hospitals and four primary care clinics) will not receive this training. Participant assessments will be conducted by researchers blinded to treatment allocation and will occur at baseline, as well as 1 week, 4 weeks, 12 weeks, and 24 weeks after their first physiotherapy appointment (see Figure 3 for an overview). The primary endpoint for analysis will be data collected at week 24. Recruitment is expected to take place from April 1, 2011 to June 15, 2012.

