#### Physiotherapists

All physiotherapists at participating sites will be informed that the trial is designed to evaluate the effect of a communication skills training program and will be invited to participate in the study. All physiotherapists practicing in publicly funded clinical settings in Ireland must be Chartered Physiotherapists. No further inclusion or exclusion criteria will be specified. Those who agree to participate will be asked to provide written consent, complete a baseline assessment, and attend a one hour education session (“Evidence-based care for CLBP management refresher workshop”). Physiotherapists will not be blinded to treatment allocation, as they are implementing the intervention with patients.

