### Primary outcomes

#### Adherence

**·****Sports Injury Rehabilitation Adherence Scale:** This questionnaire is designed to measure physiotherapists’ perceptions of their patient’s rehabilitation adherence. It has been shown to be a reliable scale for use in clinical physiotherapy [42].

**·****Adherence to Physiotherapist’s Recommendations Scale:** To measure overall levels of adherence, we will employ the two-item adherence scale previously employed by Chan et al. [26]. The scale demonstrated acceptable internal consistency in their study involving physiotherapists.

**·****Home Exercise Compliance Assessment**: To measure specific adherence to back exercise and physical activity advice we will calculate the percentage of prescribed sessions completed per week (Note: # prescribed session per week will be self-reported and confirmed from physiotherapists’ records). This measure has been previously employed in LBP studies [10].

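### A primary adherence measure is scored by unblinded treating physiotherapists, against the abstract's blinded-assessor statement, and is not scheduled at the week-24 primary endpoint

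*Protocol article*

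**What the plan says.** **The measure and its status.** In the protocol article, Primary outcome measures, item (i) combines two ratings of general adherence: one by the patient outside the clinic, and one "during the therapy session as rated by the physiotherapist", using an adapted Sports Injury Rehabilitation Adherence Scale. Appendix A lists that scale under primary outcomes and describes it so: "This questionnaire is designed to measure physiotherapists’ perceptions of their patient’s rehabilitation adherence". Hypothesis 1 predicts higher physiotherapist ratings in the experimental arm.

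**The raters.** The Physiotherapists subsection on recruitment and blinding states: "Physiotherapists will not be blinded to treatment allocation, as they are implementing the intervention with patients". It also states: "All physiotherapists at participating sites will be informed that the trial is designed to evaluate the effect of a communication skills training program".

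**The blinding statement.** The abstract, after saying that patients are blinded, adds: "Outcome assessors will also be blinded".

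**The time point.** Design overview: "The primary endpoint for analysis will be data collected at week 24". Statistical methods repeats this. Neither place makes an exception for any outcome.

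**The schedule.** Table 3 marks clinic-based adherence at post-treatment baseline and at weeks 1, 4 and 12. The week-24 cell is empty. The note to the table defines the mark as "physiotherapist rating of patient behavior following each treatment session (most likely to occur during first 12 weeks following initial session".

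**The concern.** Adherence is the stated aim of the trial, and one of its primary measures is the opinion of the people on whom the intervention acts. They know their arm and know what is being tested. A difference between arms on this scale could therefore reflect how physiotherapists score rather than what patients do. It could still be reported as a primary adherence effect from a trial described as having blinded outcome assessors. Item (i) does not rank the patient and physiotherapist ratings, so nothing in the article prevents a positive physiotherapist rating from standing alone as a primary finding.

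The timing adds a second problem. A measure with no scheduled week-24 value cannot supply the analysis named as primary, so as written one primary outcome has no defined primary analysis time.

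**Working it through.** The point rests on a comparison of statements and no stated figure needs to be reproduced.

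**Step 1: who assesses, and are they blinded?**

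| Question | Statement | Place |
|---|---|---|
| Is the measure primary? | Yes | Primary outcome measures (i); Appendix A, Adherence |
| Who scores it? | The physiotherapist, after each session | Treatment phase assessment; note to Table 3 |
| Is that person blinded? | No, in either arm | Physiotherapists (recruitment and blinding) |
| Does that person know the trial's purpose? | Yes | Same subsection |
| Are outcome assessors blinded? | Yes, unqualified | Abstract, Methods/Design |

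The physiotherapist is the outcome assessor for this scale. The second, third and fifth rows cannot all be true. Design overview and Centers also speak of blinding, but of researchers and of investigators who collect data, terms that need not cover treating physiotherapists. The clear conflict is with the abstract sentence.

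**Step 2: can the design separate rater shift from patient behaviour?** The first mark in Table 3 is in the post-treatment baseline column, that is, after the first session. An in-session rating cannot exist earlier, so there is no pre-treatment value to adjust for. If experimental-arm raters score higher or lower than control-arm raters for the same behaviour by *s* standard deviations, the expected contrast is the true difference plus *s*. A larger sample does not reduce *s*. The document gives no value for *s* and no sign.

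**Step 3: is the measure available at the primary endpoint?** Counting Table 3:

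- Clinic-based adherence: 4 columns marked (post-treatment baseline, weeks 1, 4 and 12); 0 marks at week 24.
- Rows under the primary heading: 3 adherence + 1 physical activity + 2 symptoms + 2 function + 1 well-being = 9.
- Of these 9, marked at week 24: 8. The only empty cell belongs to clinic-based adherence.

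The rating is triggered by a treatment session, and the note says that sessions fall most likely in the first 12 weeks. A late session could produce a rating near week 24, but only for a patient still attending. That is not a scheduled week-24 assessment of the trial population.

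**The case against.** **Much is disclosed.** The article calls the trial single-blinded, says openly that physiotherapists are unblinded, names them as raters and gives their ratings a separate symbol in Table 3. This stands, and it confines the blinding contradiction to one abstract sentence. It does not make that sentence correct.

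**The rest of the adherence evidence is unaffected.** General adherence and specific exercise and activity adherence are patient-reported at week 24 by patients who are not told whether their physiotherapist was trained. This also stands. A reader might infer that the whole adherence result is unblinded or unusable; it is not.

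**The measure can be analysed.** The mixed model tests mean levels and rates of change and accepts unequal numbers of ratings, so earlier ratings can be used. A measure-specific time point may exist in an analysis plan that is not shown. Even so, the article fixes week 24 twice without exception.

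**Stronger readings that the document does not support:**

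- Hypothesis 4, with its phrase "As a result of heightened self-awareness that comes from participation in communication skills training", might be read as predicting that training changes how physiotherapists score patients. It predicts only that they will rate their own autonomy support lower. It does not concern ratings of patients and cannot be used to give the bias a direction.
- The treatment record forms carry 5A prompts in the experimental arm only, and an unblinded investigator follows up omissions (Data integrity). Nothing says that the adherence items differ by arm or that queries affect scores.
- The empty cell might be read as meaning that no rating can ever occur at week 24. It means that none is scheduled.
- Any particular size for the rater shift, for example as a share of the d = .4 used for the sample size, would be pure assumption.

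**Conclusion.** The point holds for one component of primary outcome (i). The abstract's statement that outcome assessors are blinded is wrong for the physiotherapist-rated scale, and that scale has no scheduled value at the time point declared primary for every outcome. The first part follows from the article's own description of the raters; the second from Table 3 and its note. The measure is open to rater bias of unknown direction and size. The reach is limited: one of nine primary rows in Table 3 is affected, and patient-rated adherence at week 24 remains available. The conclusion assumes only that the article's text and Table 3 represent the current plan.

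**What to change.** 1. Make the physiotherapist-rated scale a secondary or process outcome, labelled as unblinded, in Primary outcome measures, Table 3 and Appendix A. Keep the hypothesis 1 comparison on it, but mark it as not primary.
2. Analyse it over attended sessions to week 12 with one summary chosen in advance, for instance the mean rating, and exempt it explicitly from the week-24 statement.
3. Keep the patient-rated adherence measures as the primary adherence outcomes at week 24.
4. Reword the abstract's blinding sentence. Patient-reported follow-up outcomes are either self-completed or collected by telephone by a blinded researcher, from patients not told their physiotherapist's training status; physiotherapist ratings of adherence are unblinded. A sentence saying simply that blinded assessors collect the patient-reported outcomes would not be accurate, because weeks 4, 12 and 24 may be completed online or by post with no assessor.

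Keeping the scale primary with its own time window and a qualified blinding sentence would reconcile the text, but would leave a primary outcome exposed to rater bias.

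Cost: wording and reclassification only. Data collection is unchanged; the one loss is that an adherence measure gives up primary status.

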### Aims

The aim of this cluster randomized controlled trial (RCT) is to assess the effect of an intervention designed to increase physiotherapists’ autonomy-supportive communication on CLBP patient’s adherence to physical activity and LBP exercise recommendations.

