### Sample size

The sample for the study was calculated using data from our recent pilot study [36]. The effect sizes observed in that investigation were *d* = .4 for adherence and satisfaction with back pain, and *d* = .5 for PA-walking behavior. These effect sizes are similar to those reported in a recent Cochrane review of trials investigating the effectiveness of interventions designed to increase adherence among chronic pain patients [16]. As a result, the estimated sample required for 80% power (α = .05) to detect a between arm effect of d = .4 in a non-clustered RCT, using a t-test, would be 156 (*n* = 78 per arm).

To account for the clustered nature of the data, we multiplied this sample size by a correction factor of 1 + (*m* − 1)ρ, where *m* was the mean expected cluster size and ρ was the anticipated intracluster correlation coefficient [38]. Based on previous research in clinical settings regarding physical activity in patients with CLBP [18,23], we estimated that the ICC would be 0.03. Assuming we recruit *m* of 22 patients per clinic, the correction factor is 1.63 for our cluster-randomized design. To account for the clustered design, the study would require 254 participants to achieve 80% power for the adherence and LBP related data.

We anticipate that approximately 15% of participants will not complete follow-up assessments [39]. Traditionally, one would account for this loss to follow up and increase the sample size by 15% to 292 participants (146 per arm). However, as our method of analysis (linear mixed models, see statistical methods section) does not require list-wise deletion, and therefore loss to follow-up is expected to have negligible impact. Indeed, Chakraborty and Gu [40] demonstrated that up to 20% of the observations can be missing without a meaningful loss of power for mixed modeling approaches. As such, our intended sample of 292 patients will provide more than 80% power to detect significant effects in these primary outcomes.

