### Statistical methods

Researchers will analyze the data using a coded dataset and these individuals will not become unblinded until analysis is complete. Participants’ data will be analyzed according to their assigned arm of the study, regardless of whether they attend their physiotherapy treatment sessions or not (i.e., intention-to-treat principle).

Fidelity of the intervention will be assessed in a subsample of patients. We will employ between-arm comparisons of autonomy support ratings made by (i) patients, (ii) physiotherapists and (iii) independent, blinded raters of audio recordings. We will also compare 5A strategy use, as measured by independent, blinded raters of audio recordings.

The main study hypotheses will be explored using linear-mixed modeling with measurement occasions, patients, physiotherapists, and clinics as potential levels of the analysis. Using a dummy-coded “treatment” variable (experimental vs. control) as a predictor in the model, we will test differences both in the mean levels and the rates of change of the primary and secondary outcome variables. The primary endpoint for the analysis will be data collected at week 24. Lastly, in order to examine the process of change, we will conduct a structural equation modeling analysis, accounting for clustering effects, to test the direct and mediated relationships outlined in Figure 2.

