#### Secondary outcomes

**·****Health Care Climate Questionnaire**: is a six-item scale used to assess autonomy support that has demonstrated good reliability and validity [49].

**·****Treatment Self-Regulation Questionnaire:** This instrument is used to assess autonomous and controlled motivation. It has demonstrated good reliability and validity across diverse health-related behaviors [50].

**·****Perceived Competence Scale:** This four-item scale has consistently produced scores with good reliability and validity in relation to a variety of health-related behaviors, including PA [32].

**·****Fear Avoidance Beliefs Questionnaire physical activity subscale:** This is a five-item self-report questionnaire that specifically focuses on participants’ beliefs about how physical activity affects their low back pain [51].

**·****Objectively-measure physical activity:** We will measure all patients’ PA using a pedometer, which are relatively inexpensive (approximately €20) and provide basic data on daily step counts. A systematic review showed that pedometer scores correlated strongly (median r = .86) with accelerometer scores for step counts [52].

**Global Perceived Effect Scale (GPE):** The GPE is an 11-point NRS that assesses the patient’s perception of recovery. It is considered to have high face validity and is often used as the reference standard against which other subjective measures are tested when assessing their measurement properties [53].

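### Ten unranked primary instruments, each tested for level and for rate of change, with one undivided alpha of .05 and no lead outcome or contrast; one instrument is primary in one place and secondary in two others

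*Protocol article*

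**What the plan says.** **The primary list.** In Outcomes, Primary outcome measures, group (i) has three adherence measures: the physiotherapist-rated clinic scale, the patient-rated general scale and the Home Exercise Compliance Assessment. Group (ii) is the short-form physical activity questionnaire. Group (iii) is the pain rating scale followed by "Pain Bothersomeness, the Roland Morris Disability Questionnaire, the Patient Specific Functional Scale, the European Quality of Life Questionnaire, and the Perception of Recovery Scale". That makes ten. Appendix A describes bothersomeness as three separate scales, which makes twelve.

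**The tests.** Statistical methods says: "we will test differences both in the mean levels and the rates of change of the primary and secondary outcome variables". The same section, like the Design overview, makes week 24 the primary endpoint.

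**The error rate.** Alpha appears once, in Sample size, as the sample "required for 80% power (α = .05) to detect a between arm effect of d = .4 in a non-clustered RCT". That section ends: "our intended sample of 292 patients will provide more than 80% power to detect significant effects in these primary outcomes".

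**The aim.** Aims speaks only of "adherence to physical activity and LBP exercise recommendations".

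**The recovery scale.** Table 3 puts "Perception of recovery" under its secondary heading. Appendix A describes the matching instrument under secondary outcomes too ("The GPE is an 11-point NRS that assesses" the patient's view of recovery).

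**The concern.** A protocol should let a reader know beforehand which result decides the trial. Here ten instruments carry equal primary status and each is examined in two ways. The week-24 statement settles when, but not which outcome or whether level or slope. With no lead outcome, a favourable result on any listed instrument could be presented as a primary finding, although the stated aim is adherence. For the recovery scale, whether a favourable result counts as primary depends on which section is cited. The power claim is also made for the primary outcomes as a group, from a calculation that spends the whole alpha once.

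**Working it through.** **1. The plan's own figure.** Inputs from Sample size: d = 0.4, alpha .05, power 80%, 22 patients per clinic, ICC 0.03, 15% loss.

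- Per arm, n = 2(z_alpha + z_power)²/d². One-sided: 2(1.645 + 0.842)²/0.16 = 77.3, so 78 per arm, which matches the text ("using a t-test, would be 156"). Two-sided: 2(1.960 + 0.842)²/0.16 = 98.1, so 99 per arm. The stated figure is therefore reproduced only with a one-sided test, and the article does not state sidedness. That is a separate matter, but it is why both versions are shown below.
- Design effect: 1 + 21 × 0.03 = 1.63; 156 × 1.63 = 254.3; 254 × 1.15 = 292.1. The chain 156 / 254 / 292 is reproduced with a single test at .05.

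**2. How many primary tests exist at week 24.** Ten are listed. In Table 3, clinic-based adherence has no week-24 mark, which leaves nine. If Perception of Recovery is secondary, eight remain. The range is 8 to 10, before bothersomeness is split.

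**3. Chance of at least one false positive, if each test is run at .05.** For k independent tests it is 1 − 0.95^k. The correlated figures use normal test statistics with one common correlation. That correlation is an assumption, since the article gives none.

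| Tests | Independent | rho .5, two-sided | rho .8, two-sided |
|---|---|---|---|
| 8 | 33.7% | 25% | 16% |
| 9 | 37.0% | 27% | 17% |
| 10 | 40.1% | 29% | 17% |
| 12 | 46.0% | 32% | 19% |

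One-sided figures are a little lower: for ten tests, 25% at rho .5 and 15% at rho .8. At rho .9, ten two-sided tests give 13%.

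**4. Counting level and slope separately.** Twenty independent tests give 1 − 0.95^20 = 64%, and 24 give 71%. These are upper bounds, because level and slope of one outcome come from the same patients. With rho .5 to .8 between instruments and 0 to .8 between level and slope, twenty two-sided tests give 26% to 49%.

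**5. What alpha control would do to power.** Power is Φ(d·√(n_eff/2) − z), with n_eff = 146/1.63 = 89.6 per arm, so d·√(n_eff/2) = 2.677 (all 292 analysed).

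| Alpha per test | One-sided | Two-sided |
|---|---|---|
| .05, one primary outcome | Φ(2.677 − 1.645) = 85% | Φ(2.677 − 1.960) = 76% |
| .005, Bonferroni over ten | Φ(2.677 − 2.576) = 54% | Φ(2.677 − 2.807) = 45% |

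**6. The recovery scale.** Primary outcome measures calls it primary, while Table 3 and Appendix A call it secondary. Outcomes refers the reader to Table 3 and Appendix A for timing and description, so all three are current text.

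**The case against.** The strongest reply is that this is a journal article without its analysis plan, and that testing order, multiplicity adjustment and per-test alpha usually belong in that plan. That is right as far as it goes: the absence of a multiplicity rule is not by itself a fault here. What the article does fix is an unranked list of ten primaries, two tests for each, and one instrument with contradictory status. A later plan that named a lead outcome would have to change that stated list.

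Several stronger readings are tempting, and the text does not support them:

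- *Any single positive primary makes the trial a success.* No such rule is written; it is only not excluded. The hypotheses separate adherence and activity from pain, function and well-being, and the aim names adherence alone.
- *Each outcome is tested at .05.* Alpha is given only for the sample size. Its use for each test is an inference, though no other level appears.
- *The false-positive chance is 71%.* This treats 24 tests as independent, including level and slope of the same outcome. Nor does the article call the slope a primary claim.
- *The sample size points to one adherence scale.* It rests d = 0.4 on adherence and on satisfaction with back pain. Appendix A ties specific adherence to exercise and activity advice, the wording closest to the aim, to the Home Exercise Compliance Assessment.
- *Perception of Recovery simply belongs with the secondaries.* Hypothesis 2 groups perceived global improvement with pain and function. The secondary outcome section describes explanatory variables and does not name recovery. The direction is open.

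**Conclusion.** The concern holds in limited form. The protocol fixes ten unranked primary instruments (twelve if bothersomeness is split) and two tests for each, with one undivided alpha and no lead outcome or contrast. One listed primary cannot be assessed at the stated primary time point.

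If each were tested at .05, the chance of at least one false-positive primary result at week 24 would be about 34–40% for 8 to 10 independent tests, and about 16–29% at correlations of .5 to .8. That is roughly three to eight times a nominal 5%. It rests on the inferred per-test alpha, two-sided tests and assumed correlations. Figures for 20 or more independent tests are upper bounds only.

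The conflicting status of Perception of Recovery needs no assumptions.

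**What to change.** Before analysis:

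1. Name one lead primary outcome and one contrast, the between-arm difference at week 24. Choose it from the adherence measures that match the aim and have week-24 data. Patient-rated general adherence is one suitable candidate; the Home Exercise Compliance Assessment also meets both conditions.
2. Put the other listed outcomes under a fixed testing order or Holm control, or label them secondary.
3. Give Perception of Recovery the same status in Primary outcome measures, Table 3 and Appendix A.
4. If several primaries are kept with alpha control, restate the more-than-80% power claim for the adjusted alpha.

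The cost is wording; no new data are needed. The downside is small: some outcomes lose unadjusted primary status.
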